### Advice and education

Participants in each group will be given standardised information about Achilles tendinopathy, pathology, aetiology and management via a pamphlet. They will be informed that they will most likely experience muscle soreness within the first 2 to 4 weeks of the exercise program (delayed onset muscle soreness and/or fatigue) and given information about how to manage soreness. Participants will be requested to refrain from other forms of treatment during the study period. If they require medications for their Achilles tendon pain, they will be advised to consume up to 4 g/day pain-relieving medication, such as paracetamol or acetaminophen [32].

### Videoconference exercise monitoring

Exercise adherence and fidelity are critical to assess our aim of comparing exercise parameters between groups. To maximise this, we have developed a telerehabilitation protocol to monitor participants weekly. A practising physiotherapist (videoconference care provider) will be allocated to each participant at baseline and supervises exercise via a weekly videoconference session using Zoom (Zoom Video Communications, San Jose, California) for 12 weeks. The telerehabilitation protocol has been developed after extensive piloting to determine optimal camera position and angle, and the type of tripod suitable for the various Smith machines used in commercial gymnasiums. Bluetooth headphones will be supplied to participants and used during videoconferences, given the potential for disruptive noise in gymnasium environments.

During each weekly session, the videoconference care provider will collect adherence, health-care use, and adverse events data via questionnaire (Fig. 1). They will also observe and record the first set of each exercise—standing and seated on the right and left sides—without providing any feedback, assessing exercise fidelity. Real-time feedback will be provided during subsequent sets. Care providers will undergo 12 h of training using a variety of methods: one-to-one, online materials, and a group tendinopathy management master class covering up-to-date research and clinical perspective, as well as learning comprehensive rehabilitation strategies. They will also be provided with open access tendinopathy online training supervision materials, such as demo videos and screencasts.

### Primary feasibility outcomes: study processes

The following outcomes will be used to determine the feasibility of study processes for a randomised trial:
(i)Conversion, recruitment and retention rates. Conversation rate is the proportion of participants providing consent of those who met the selection criteria. Recruitment is the number of participants recruited per month. Retention is the proportion of recruited participants who complete the 12-week outcome assessment (primary endpoints).(ii)Exercise adherence and fidelity. Exercise adherence and fidelity will be assessed from the information recorded by physiotherapists at weekly videoconference sessions. Adherence to exercise will be expressed as the percentage of prescribed exercise sessions completed or attempted per week. Exercise fidelity will be expressed as the percentage of the following key dose parameters: appropriate tempo per contraction, volume [repetitions and sets], intensity [failure +/−1 repetition].(iii)Adverse events. The frequency (number of participants and number of cases), nature (e.g. rolled ankle, muscle tear or tendon pain worsening) and severity (mild, moderate or severe) will be recorded at each weekly videoconference session. People experiencing adverse events will be managed by the research team or triaged to an appropriate medical facility. The frequency of the use of paracetamol medication and other co-interventions to relieve Achilles pain will be also recorded.(iv)Feasibility to collect economic outcomes. This will inform the decision to use an economic evaluation in a future definitive randomised trial. Health-related work productivity [33], as well as health-care use—namely current medications and treatment for Achilles—will be assessed at weekly intervals via a questionnaire during videoconference sessions.(v)Participants’ and telerehabilitation care providers’ experiences with the interventions. At the end of the intervention period, two to three participants from each group will be invited to share their experience—the acceptability of interventions, and barriers and enablers to adherence—via qualitative interviews that will last for approximately thirty minutes. A focus group will be used to assess the views of videoconference care providers.

### Secondary clinical outcome measures

To obtain a wide variety of clinically relevant information regarding treatment effects, there are a number of secondary outcome measures: pain severity, health-related quality of life, perceived treatment response, physical activity, and psychological factors. These will be determined using patient self-reported questions at baseline, 6 and 12 weeks. Change in neuromuscular plantarflexor function will be assessed before and after 12 weeks of intervention. These outcomes were informed by core outcomes domains in tendinopathy process that two of the authors were involved with (PM, BV) [34].

(i) Pain and disability: The severity of pain and disability will be assessed using VISA-A, a disease-specific tool with acceptable construct validity and test-retest reliability [35]. This outcome includes pain, function and activity domains, the total score ranging from zero to one hundred (the latter indicating no symptoms and full function). One limitation of the VISA-A questionnaire is that it is designed for athletes. More specifically, the eighth question of the VISA-A, comprising up to 30% of the maximum possible score, is not applicable to non-athletes. As participants are athletes and non-athletes, we will use the original version of the VISA-A and a modified version of the VISA-A designed to be used for both athletes and non-athletes [36]. In the modified version, the word ‘sport’ has been replaced with ‘physical activity’, ensuring relevance to both sporting and non-sporting populations. We will subsequently assess the sensitivity to change of each version.

(ii) Activity pain: The worst pain imaginable level participants experience in the last week of the study will be assessed with an eleven-point rating scale, with zero being no pain and ten being the worst possible pain.

(iii) The patient impression of change: This will be assessed with the Patient Global Impression of Change (PGIC). A seven-point Likert scale is used to rate two questions: “How would you describe your Achilles tendon pain now, compared to before you began the treatment?”, and “How would you describe your ability to perform physical activities (such as walking, running, housework) now, compared to before you began the treatment?” For analysis purposes, the PGIC will be dichotomised so that “very much improved” and “improved” represents treatment effectiveness.

(iv) Participant satisfaction: Participant satisfaction or acceptability of symptom status will be measured using the Patient-Acceptable Symptom State instrument [37]. Participants will be asked: “Currently, are you satisfied with your condition?”, and “Would you recommend this treatment to another person who has Achilles pain?” Possible responses are yes or no.

(v) Health-related quality of life: This will be measured using the five-level EQ-5D version (EQ 5D 5 L), a validated and reliable tool among people with musculoskeletal pain [38]. The EQ 5D 5 L includes five domains—mobility, self-care, usual activities, pain/discomfort, and anxiety/depression—on a five-point Likert scale, and a rating of overall health state from zero (worst health state imaginable) to one hundred (best imaginable health state) using a VAS.

(vi) Level of physical activity: Participants’ physical activity will be measured using the seven-day Physical Activity Recall Questionnaire (PAR) [39], a valid and reliable measure of health-related physical activity behaviours in the previous seven days. The PAR has been used to assess physical activity behaviours in musculoskeletal and chronic pain populations [40].

(vii) Work productivity: This will be assessed with the Work Productivity and Activity Impairment Questionnaire (WPAI) that measures workdays lost. The WPAI is validated to measure impairments in work and activities [41]. The direct and indirect cost associated with delivery of the intervention may be an important measure for clinical decision making in Achilles tendinopathy rehabilitation.

(viii) Fear of movement: Kinesiophobia, or fear of movement/re-injury, will be measured with the Tampa Scale for Kinesiophobia (TSK) [42]. This questionnaire consists of seventeen statements rated on a four-point Likert scale (strongly disagree, disagree, agree, strongly agree). The total score ranges from 17 to 68, with higher scores indicating greater fear of movement.

(ix) Pain catastrophising: This will be measured using the Pain Catastrophising Scale (PCS) [43]. The PCS consists of thirteen items rated on a five-point Likert scale (not at all, to a slight degree, to a moderate degree, to a great degree, all the time) evaluating the degree to which participants experience catastrophic thoughts or feelings. The total score ranges from zero to 52, with higher scores indicating higher levels of pain catatrophisation.

(x) The exercise load (kg) for both seated and standing during calf raise exercises will be assessed at each weekly videoconference session. Set workload as a proportion of body mass (%) will be calculated through the 12 weeks of intervention (load (kg) × reps × time × sets = one exercise session).

### Sample size estimation

A formal sample size calculation was not performed, as this is a feasibility study and not subjected to hypothesis testing. Instead, we made a pragmatic decision that we would be able to achieve our secondary aim by recruiting forty-eight participants to be randomised into one of four factorial arms (*n* = 12 per trial arm as a rule of thumb recommended by Julious [44]).

### Data management and analysis

Both feasibility and clinical outcome data will be transferred to Excel spreadsheets, which will then be combined into one database. Quality checking for data entry will be performed by visually inspecting data and creating frequency tables for all items by two members of the research team. All data will be de-identified with analyses performed by an independent analyst. The randomisation code will not be broken until the final follow-up measurement has been performed (i.e. participant’s last visit), and data analysis has been completed. Both hard and soft copy data will be protected and accessible only to the research team. The principal investigator will have access to the final datasets. Results will be made available to participants on request and will be published in a peer-reviewed journal.

Means and standard deviations (or medians and IQRs, where data is not normally distributed), mean or median differences and their 95% confidence intervals of all outcome measures will be calculated at each follow-up time. Point estimates of effect will be calculated as the difference between group means expressed as a proportion of the pooled standard deviation. The effect size criteria will be interpreted as per Hopkins [45], with very large being ≥1.2, moderate being ≥0.6, and small being ≥0.2. Standard tests to assess continuous data for normal distribution will be used and transformation will be carried out if required for further analysis.

The MVIC force data (Nm) will be analysed directly from PowerLab (AD Instruments Corp, Dunedin, NZ) for each recorded trial. RFD data (N·s-1) and force match data will be exported to Excel (Microsoft Corporation, Redmond, WA). The RFD will be analysed using a custom-written software program (rehabtools.org, Sunshine Coast, Australia). For the FM task, a sample of force (from five to fifteen seconds during each trial) will be obtained to calculate the mean and coefficient of variation (CV) of force (SD/mean force % 100).

The trial will be deemed a success based on the following:
(i)Randomising 20% or more of eligible patients that fit the selection criteria.(ii)Achieving 66% or more of the number of sessions completed in each group.(iii)Achieving 66% or more of intervention fidelity (i.e. prescribed dose parameters including tempo, volume, and intensity in each group).(iv)Report of ≤5% of serious adverse events.

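### The single mean/median and pooled-SD rule for all outcome measures does not suit the four yes/no secondary items (dichotomised PGIC and satisfaction)

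*Protocol article*

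**What the plan says.** Under Data management and analysis, the protocol article gives one summary rule. Outcomes are described by means and standard deviations, "or medians and IQRs, where data is not normally distributed", and then "mean or median differences and their 95% confidence intervals of all outcome measures will be calculated at each follow-up time". The effect measure follows: "Point estimates of effect will be calculated as the difference between group means expressed as a proportion of the pooled standard deviation". It is graded on a published scale, "with very large being ≥1.2, moderate being ≥0.6, and small being ≥0.2". No outcome is exempted from these sentences. Only the next sentence is limited by data type: "Standard tests to assess continuous data for normal distribution will be used".

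Under Secondary clinical outcome measures, item (iii) has two PGIC questions on a seven-point scale and states that for analysis "the PGIC will be dichotomised so that “very much improved” and “improved” represents treatment effectiveness". Item (iv) has two satisfaction questions, of which it says "Possible responses are yes or no". Four clinical items are therefore binary when they reach the analysis. The article states no summary or between-group measure based on proportions for them.

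**The concern.** This is a stated rule whose scope is too wide, not a detail left for later. A difference in means divided by a pooled standard deviation is meant for continuous scores. For a yes/no item, the standard deviation is fixed by the proportion itself, so the standardised effect mixes the size of the gap with its position on the 0 to 1 scale. The small, moderate and very large labels then cannot be compared between items or time points. A median of yes/no data is cruder still: in an arm of 12 it can only be 0, 0.5 or 1.

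The Aims section names participant perception of change and satisfaction among the outcomes for which trends in effect and variability are to be explored. What a later trial needs from the pilot on these items is response proportions and honest intervals around their differences. Banded standardised effects do not supply that.

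**Working it through.** **Inputs.** Sample size estimation gives 48 participants in four arms, 12 per arm (4 × 12 = 48), so 24 per level of each factor. The article gives no response rates for the binary items; all counts and rates below are illustrative assumptions.

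**1. Mean branch.** For 0/1 data the mean is x/n and the mean difference is the risk difference. For 10/12 v 7/12 it is 0.833 − 0.583 = 0.25 by either name. The pooled t interval is −0.14 to 0.64; the Newcombe interval is −0.11 to 0.54. By exact enumeration at 12 per arm, for four pairs of true rates 20 points apart (0.6 v 0.4 up to 0.9 v 0.7), the t interval covers the true difference with probability 0.938 to 0.963. It weakens near the boundary:

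- true rates 0.95 v 0.85: coverage 0.844 (Newcombe 0.994);
- 12/12 v 2/12: t interval 0.60 to 1.07, with an impossible upper limit (Newcombe 0.46 to 0.95);
- 12/12 v 12/12: t interval of zero width (Newcombe −0.24 to 0.24).

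**2. Standardised effect.** With equal arms, d = (p1 − p2) / sqrt[(v1 + v2)/2], where v = p(1 − p) × n/(n − 1).

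- 7/12 v 5/12: v1 = v2 = 0.2431 × 12/11 = 0.265; pooled SD 0.515; d = 0.1667/0.515 = 0.32, small.
- 12/12 v 10/12: v1 = 0, v2 = 0.1389 × 12/11 = 0.152; pooled SD 0.275; d = 0.1667/0.275 = 0.61, moderate.
- 12/12 v 12/12: 0/0, undefined.

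The same happens with a fixed gap of 25 points:

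| Counts | d | Label |
|---|---|---|
| 8/12 v 5/12 | 0.50 | small |
| 10/12 v 7/12 | 0.55 | small |
| 11/12 v 8/12 | 0.62 | moderate |
| 12/12 v 9/12 | 0.78 | moderate |

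Pooling to 24 per factor level does not remove it: 15/24 v 9/24 gives 0.51 and 24/24 v 18/24 gives 0.80. In terms of true rates, a 20-point gap gives d = 0.41 at 0.6 v 0.4, 0.52 at 0.9 v 0.7 and 0.67 at 0.99 v 0.79. For a gap of that size the label changes only at high response rates.

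**3. Median branch, if it were used.** The median of 12 values is the average of the 6th and 7th in order.

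- 7/12 v 5/12: medians 1 and 0, difference 1, against a risk difference of 0.17.
- 10/12 v 7/12: medians 1 and 1, difference 0, against a risk difference of 0.25.
- True rates 0.8 v 0.6: the median difference is 0 with probability 0.66 at 12 per arm and 0.79 at 24 per factor level.

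**The case against.** The best defence is that a sensible analyst would never take medians of yes/no answers. The normality checks are expressly for continuous data, so nothing clearly sends a binary item to the median branch. On the mean branch the numbers are right. Defining a PGIC responder category itself suggests that a responder rate is intended, and a fuller analysis plan may say so. The study plans no hypothesis tests, and no decision turns on the effect-size labels.

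Much of this stands. It makes the median results conditional, and it rules out several stronger readings:

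- A reader might infer that the rule gives wrong values for all binary outcomes, or leaves the pilot without usable proportions. It does not: the mean branch yields both the proportion and the risk difference.
- A reader might extend the point to retention. The section on primary feasibility outcomes already settles that: "Retention is the proportion of recruited participants who complete the 12-week outcome assessment". It is a study-process measure, not a treatment effect repeated at each follow-up.
- A reader might add that cutting the PGIC from seven levels to two wastes a known share of information. That share depends on category frequencies that the article does not give, and no test or power claim rests on it.

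The defence does not rescue the standardised effect. It is the only effect measure stated, the sentence carries no limit to continuous outcomes, and the summary rule beside it explicitly covers all of them. A later plan that used proportions for these items would be correcting the published text, not filling a gap in it.

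**Conclusion.** The point holds for four secondary items: two PGIC questions and two satisfaction questions. The pooled-SD effect and its bands do not suit them: in the examples a fixed gap of 17 or 25 points moves from small to moderate with the base rate alone, and the measure has no value when all respond in both arms. Mean-based intervals are adequate at middling rates and unreliable near 0 or 1. The median problem arises only if the non-normality switch is applied to these items, which the text neither clearly requires nor excludes.

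The consequence is limited. It concerns the exploratory secondary objective, and none of the four success criteria (randomisation of eligible patients, sessions completed, fidelity, serious adverse events) uses these items. How often the labels would mislead depends on response rates that are assumed here.

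**What to change.** Limit the mean/median summary, the pooled-SD effect and its bands to continuous outcomes. For each PGIC question and each satisfaction question, report n/N and percentage by arm and by factor level, with risk differences and a 95% interval suited to small samples, such as Newcombe's, and apply no effect-size bands. For the illustrative counts this gives 0.17 (−0.21 to 0.48) for 7/12 v 5/12, 0.25 (−0.11 to 0.54) for 10/12 v 7/12, and 0.00 (−0.24 to 0.24) for 12/12 v 12/12, so the case that the standardised effect cannot handle gets a usable interval.

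The cost is two sentences in the analysis section and a few extra table rows. No new data are needed, and the PGIC responder definition can stay as it is.

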### Aims

This study aims to assess the feasibility of a future definitive randomised trial to examine the efficacy of different LOAD-intensity and time-under-tension (LOADIT) exercise parameters for Achilles tendinopathy. The primary objective is to assess the feasibility of study processes, including (i) rate of participant recruitment, conversion, and retention; (ii) ability to perform the interventions per protocol (adequate exercise fidelity and adherence based on weekly assessment via videoconferencing mode); (iii) incidence and type of adverse events; (iv) feasibility of future economic evaluation; and (v) acceptability of telerehabilitation videoconference sessions. The secondary objective is to explore trends in treatment effects and variability—in pain and disability, participant perception of change, satisfaction, health-related quality of life, physical activity, work absenteeism, psychological measures, and plantar flexion contractile dysfunction—between the groups at 6 and 12 weeks. These time points have been selected based on evidence that exercise effect should be maximised at 12 weeks [18].

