A factorial design has been chosen for two main reasons. First, it is not possible to compare load in a two-arm design without one other characteristic varying. If one group performed four sets of six repetitions and the other performed four sets of eighteen, then the time-under-tension is greater in the latter group. This can be controlled by asking the second group to also perform four sets of six at an eighteen RM intensity; however, the varying factor then becomes whether people are achieving fatigue or not. The factorial design allows researchers to have two groups matched for time-under tension. Second, the factorial designs allow comparison of outcomes of a different combination of time-under-tension and load intensity. We recognise that in this feasibility pilot, we are not powered to investigate effects between the different groups, but it is important to justify our choice of factorial design.

The outcome measures we will use in this trial have been informed by the recent development of a core outcome set for tendinopathy that two of the authors were involved with. We have included outcomes reflecting all of the core outcome domains, including a validated and disease-specific pain and disability outcome (VISA-A). Two versions of the VISA-A will be included: the original, and an amended version that may be more suitable to non-athlete participants.

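### Magnitude labels are read off the point estimate of d without its uncertainty, so at 12 per arm a label alone says little about a real difference (minor)

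*Protocol article*

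**What the plan says.** Under Data management and analysis, the protocol plans means and standard deviations (or medians and interquartile ranges) and mean or median differences with 95% confidence intervals, for all outcomes at each follow-up. It then defines a standardised effect: "Point estimates of effect will be calculated as the difference between group means expressed as a proportion of the pooled standard deviation". The next sentence says how that effect is to be read: "The effect size criteria will be interpreted as per Hopkins [45], with very large being ≥1.2, moderate being ≥0.6, and small being ≥0.2". No interval is mentioned for the standardised effect, and no label depends on the interval for the raw difference.

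The sample is set under Sample size estimation at "12 per trial arm as a rule of thumb", 48 in all. That section adds: "A formal sample size calculation was not performed, as this is a feasibility study and not subjected to hypothesis testing". The Aims section frames the clinical part as exploratory: "The secondary objective is to explore trends in treatment effects and variability". The Discussion concedes that "we are not powered to investigate effects between the different groups".

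**The concern.** The cut-offs are the only stated rule for interpreting the clinical comparisons, and their one input is the estimated d. With 12 per arm the standard error of d is about 0.41 when there is no true difference, roughly twice the lowest cut-off. Sampling variation alone will therefore often carry the estimate past 0.2, and sometimes past 0.6.

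At stake is how the secondary results are read. A dose comparison that is compatible with no difference can appear in the report as a 'small' or 'moderate' effect. That sits badly with the Discussion's own statement that the pilot cannot investigate differences between groups.

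**Working it through.** **Inputs from the protocol.** 48 participants in four arms, so 48 / 4 = 12 per arm (Sample size estimation). A 2 × 2 factorial (Trial design), so comparing the two levels of one factor sets 24 against 24. Cut-offs of 0.2, 0.6 and 1.2 for d (Data management and analysis). The protocol states no power, alpha or labelling rate, so the only figure of its own to reproduce is 4 × 12 = 48, which agrees.

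**Assumptions.** Normal outcomes, equal standard deviations, no true difference, everyone analysed, and labels applied in either direction. No dropout rate is stated, so 10 and 8 analysed per arm are shown as a range.

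**Formula.** With n per group and no true difference, d / √(2/n) follows a t distribution on 2n − 2 degrees of freedom. So P(|d| ≥ c) = 2 × P(t ≥ c / √(2/n)).

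**12 v 12.** √(2/12) = 0.408, with 22 degrees of freedom.
- c = 0.2: t = 0.2 / 0.408 = 0.490, probability 62.9%
- c = 0.6: t = 0.6 / 0.408 = 1.470, probability 15.6%
- c = 1.2: t = 1.2 / 0.408 = 2.939, probability 0.8%

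By label: 'small' only, 62.9 − 15.6 = 47.3%; 'moderate', 15.6 − 0.8 = 14.8%; 'very large', 0.8%; no label, 100 − 62.9 = 37.1%. Of the labels given, 47.3 / 62.9 = 75% are only 'small'. Simulating 200,000 trials gave 63.0% and 15.6% for the first two cut-offs.

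**Other group sizes.**

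| Comparison | ≥ 0.2 | ≥ 0.6 | ≥ 1.2 |
|---|---|---|---|
| 8 v 8 (assumed losses) | 69.5% | 25.0% | 3.1% |
| 10 v 10 (assumed losses) | 66.0% | 19.6% | 1.5% |
| 12 v 12 | 62.9% | 15.6% | 0.8% |
| 24 v 24 | 49.2% | 4.3% | 0.01% |

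**What an interval would show.** Exact 95% intervals for an observed d at 12 v 12, from the non-central t distribution:
- d = 0.2: −0.60 to 1.00
- d = 0.6: −0.23 to 1.41
- d = 1.2: 0.31 to 2.06

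The interval excludes zero only when |d| exceeds 2.074 × 0.408 = 0.85 at 12 v 12, or 2.013 × 0.289 = 0.58 at 24 v 24. At 12 v 12, then, every 'small' label and every 'moderate' label below 0.85 goes with an interval that includes zero.

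**The case against.** The strongest reply is that the labels are descriptive. The protocol says that it tests no hypotheses, so calling an observed d of 0.25 'small' describes the observation and does not claim that a true difference exists. This stands in part: the 63% is not a type I error rate and should not be presented as one. But the protocol calls these quantities estimates of effect, and a scale that interprets an estimate without its precision invites the reading that an effect of that size was found.

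Second, uncertainty is already reported and disclaimed: raw differences carry 95% intervals, the aim is exploratory, and the lack of power is admitted. This softens the consequence considerably. It does not connect the label to the interval, so a 'moderate' label can stand beside an interval that includes zero.

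Third, 12 v 12 is the less favourable contrast, and a factorial would naturally compare 24 with 24. There a chance 'moderate' label falls to 4%, though 'small' or more is still reached 49% of the time. A reader might go the other way and count all six pairs of arms, which would give at least one label on a null outcome 96% of the time. The protocol does not specify those six comparisons, so that figure cannot be charged to it.

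Fourth, a reader might infer that the labels will choose arms or set the target difference for the definitive trial. Nothing in the protocol says so. All four success criteria concern feasibility: randomisation rate, sessions completed, fidelity and serious adverse events.

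Finally, the source cited for the cut-offs is not at hand and may discuss uncertainty. The point here rests only on the rule as the protocol states it.

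**Conclusion.** The point holds as a minor one. The stated rule grades d from its point estimate alone. With no true difference, normal outcomes and full follow-up, a 12 v 12 comparison reaches 'small' or more 63% of the time and 'moderate' or more 16%; at 24 v 24 the figures are 49% and 4%. Losses to follow-up would raise them. A label on its own is therefore weak evidence of a real difference between dose regimens.

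The feasibility conclusions and the planned descriptive statistics are unaffected. What needs correcting is how the secondary clinical results are read.

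**What to change.** In Data management and analysis, replace the sentence on the cut-offs with wording such as: 'Each standardised difference will be reported with its 95% confidence interval. Magnitude will be interpreted from the range of values that the interval covers, with 0.2, 0.6 and 1.2 as reference points, and not from the point estimate alone. Where the interval includes zero, the effect will be described as unclear.' Keep the planned means, standard deviations, raw differences and their intervals.

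A stricter rule, giving a label only when the whole interval lies beyond that label's cut-off, is not advised. With the approximate interval d ± 2.074 × √(2/12 + d²/48) at 12 v 12, 'small' would need an observed |d| of about 1.11, and a true d of 0.6 would earn any label in the right direction only about 13% of the time.

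The cost is a sentence or two and one interval per standardised difference, with no new data or participants. The small downside is that most clinical comparisons will be described as unclear. At 12 v 12 that would be 95% of them with no true difference, and about 71% with a true d of 0.6 (non-central t on 22 degrees of freedom, non-centrality 0.6 / 0.408 = 1.47, which exceeds 2.074 in size about 29% of the time).

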### Participant recruitment and eligibility criteria

Participants will be recruited via social media (i.e. Facebook, Twitter), and by posting study information on appropriate websites (e.g. running clubs and forums), at local community centres, senior citizen centres and sports clubs. Health professionals in Melbourne that manage Achilles tendinopathy will be asked to refer potentially eligible participants. The recruitment window is anticipated to be 6 to 8 months.

Respondents will be initially screened via telephone or email by researchers. Potentially eligible participants that satisfy the selection criteria will be provided with study information electronically and given at least 48 h to decide whether they would like to proceed.

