## Trial Status

The trial commenced in July 2018; recruitment for the study is ongoing. The trial is funded to run up to 2020.

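### The pilot's success rule has no threshold for recruitment per month or 12-week retention, although both are defined as primary feasibility outcomes

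*Protocol article*

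**What the plan says.** The Aims section puts "rate of participant recruitment, conversion, and retention" first among the components of the primary objective. The section on primary feasibility outcomes repeats the trio as its item (i), "Conversion, recruitment and retention rates", and defines each. Conversion (misprinted) is given as "Conversation rate is the proportion of participants providing consent of those who met the selection criteria". For accrual, "Recruitment is the number of participants recruited per month". For follow-up, "Retention is the proportion of recruited participants who complete the 12-week outcome assessment (primary endpoints").

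The planned pace is set out under Participant recruitment and eligibility criteria: "The recruitment window is anticipated to be 6 to 8 months". Sample size estimation gives the target as 48, in four arms of 12.

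The decision rule is in Data management and analysis. It opens with "The trial will be deemed a success based on the following" and gives four numbered criteria:

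- (i) at least 20% of eligible patients randomised;
- (ii) at least 66% of sessions completed in each group;
- (iii) at least 66% intervention fidelity;
- (iv) serious adverse events of no more than 5%.

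**The concern.** The pilot exists to show whether an adequately powered trial can be run. Too few participants per month and too few seen at the endpoint visit are two of the things it sets out to measure for that purpose, yet neither enters the rule that delivers the verdict. Of the three rates in outcome (i), only conversion has a counterpart in the rule, and that counterpart is a proportion with no time element.

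This is not a detail that an article would leave to a longer document. The article prints the rule itself, with numerical cut-offs. Followed as written, the rule can return a success for a pilot whose accrual or follow-up would not support the definitive trial.

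**Working it through.** **Inputs.** 48 participants, 12 per arm (Sample size estimation); a window of 6 to 8 months (Participant recruitment and eligibility criteria); three sessions a week for 12 weeks (Interventions, Table 1); cut-offs of 20% and 66% (Data management and analysis). The stated sample size reproduces: 4 × 12 = 48. No power calculation is claimed, so there is none to check.

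**Step 1: match outcomes to criteria.**

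| Outcome (i) component | Criterion in the success rule |
|---|---|
| Conversion | (i), 20% of eligible randomised (the outcome counts consent, the criterion counts randomisation) |
| Recruitment per month | none |
| Retention at 12 weeks | none directly; (ii) may act indirectly |

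**Step 2: recruitment.** The planned pace is 48/8 = 6 to 48/6 = 8 per month. Criterion (i) is met with 48 randomised as long as no more than 48/0.20 = 240 patients were eligible. Time does not enter. If 48 took 12, 18 or 24 months, the pace would be 4.0, 2.7 or 2.0 per month, and criterion (i) would give the same answer each time. These durations are illustrations.

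**Step 3: retention, if dropouts' missed sessions count.** Each participant is prescribed 3 × 12 = 36 sessions, so an arm of 12 is prescribed 432. The criterion needs 0.66 × 432 = 285.1, that is, 286 sessions. Suppose k participants leave after week w and everyone attends fully until then. Sessions completed are (12 − k) × 36 + k × 3w.

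| Dropout time | Largest k that passes | Sessions completed | Share | With one more lost |
|---|---|---|---|---|
| At the start | 4 | 8 × 36 = 288 | 66.7% | 252/432 = 58.3%, fails |
| After week 4 | 6 | 6 × 36 + 6 × 12 = 288 | 66.7% | 264/432 = 61.1%, fails |
| After week 6 | 8 | 4 × 36 + 8 × 18 = 288 | 66.7% | 270/432 = 62.5%, fails |
| After week 8 | 12 | 12 × 24 = 288 | 66.7% | no more to lose |

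In the last row 12-week retention could be zero with criterion (ii) met.

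Less than full adherence tightens the limit. With completers attending 90%, 80% or 75% of sessions, the tolerated loss at the start falls to 3, 2 or 1 of 12: 9 × 0.90/12 = 67.5%, 10 × 0.80/12 = 66.7%, 11 × 0.75/12 = 68.8%. Late loss can still pass: with 80% attendance throughout and 6 of 12 leaving after week 8, the total is 0.80 × (6 × 36 + 6 × 24) = 288, again 66.7%.

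**Step 4: retention, if only participants on study count.** Sessions missed after dropout leave the denominator, and criterion (ii) puts no limit on dropout. The outcome definition expresses adherence as a percentage of prescribed sessions per week and does not say which denominator applies after someone leaves.

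**Step 5: sessions are not assessments.** Session data come from weekly videoconferences, whereas retention depends on the 12-week assessment. A participant can complete all 36 sessions and miss that assessment. This counts fully towards criterion (ii) and against retention.

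**The case against.** The strongest reply is that criterion (ii) does guard retention. A reader might infer from the missing threshold that the rule returns a success whatever the retention. The documents do not support that. Adherence is defined against prescribed sessions, and if dropouts' missed sessions count, losing half an arm at the start caps completion at 50% and fails. With half lost and completers attending everything, the dropouts must still average (285.12 − 6 × 36)/6 = 11.5 of 36 sessions, or 32%. With completers at 80%, they must average (285.12 − 6 × 28.8)/6 = 18.7 sessions, or 52%. So early dropout is restrained under that reading. Late dropout is not, and the reading itself is not fixed.

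A reader might also infer that recruitment has in fact run far behind plan, because Trial Status says "The trial commenced in July 2018; recruitment for the study is ongoing" in an article published in July 2020. That sentence is undated. It could have been written well before publication, so no actual accrual rate can be derived from it. The gap in the rule does not depend on it.

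A third reply is that the rule is not said to be exhaustive. The abstract and the outcomes section name recruitment and retention as indicators of feasibility, both will be collected, and the economic and acceptability outcomes have no threshold either. That stands in part: poor accrual or follow-up would be visible in the report, and the outcomes are not ignored. But recruitment and retention are rates that take a threshold as readily as conversion, and the only stated verdict leaves them out.

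**Conclusion.** The point holds at moderate severity. Two of the three rates in the first-listed primary feasibility outcome have no bearing on the stated success rule. For recruitment the gap is complete: no pace, however slow, can fail the rule. For retention it is partial. With full attendance until dropout and missed sessions counted, the rule tolerates losses per arm from 4 of 12 at the start to 12 of 12 after week 8; with an on-study denominator it sets no limit.

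This assumes that the four listed criteria are the rule and that meeting them gives the success label, which is how the text reads. The omission biases no estimate and loses no data. It affects the feasibility verdict and the decision that follows from it.

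**What to change.** In Data management and analysis:

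- Add a recruitment criterion tied to the protocol's own window: at least 6 participants per month (48 in 8 months).
- Add a 12-week retention criterion as a proportion of those randomised, with a threshold chosen and justified by the sponsor. The documents give none. As an illustration only, 80% would need 39 of 48 (81.3%; exact 95% CI 67% to 91%).
- State that criterion (ii) takes as its denominator all prescribed sessions of all randomised participants.
- Report each criterion with its 95% CI.
- State that missing either new criterion means the definitive trial is redesigned before it proceeds.

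Overall recruitment and retention can be seen without knowing allocation, so setting the thresholds before unblinding would not protect them. If they are set after those data have been seen, declare them as added later.

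The cost is a few sentences, with no new data collection. The downside is that a less favourable verdict becomes possible.
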